**Fig. 1 Fig1:**
[figure not shown]
Study design including four follow-ups over a period of 6 months

On the *first day* (T1/baseline assessment; e.g. Monday), all individuals are comprehensively informed about the goals of the proposed study and all study-related measures. Individuals will give their written informed consent and will receive a copy of the relevant study information and consent agreement. Subsequently, diagnostic interviews will be performed to assess eligibility for study participation, pre-existing conditions (mental, neurological and somatic in nature), validate the diagnoses of SUD, and assess current consumption habits. Pregnancy and drug tests will also be completed. Eligible participants will be asked to complete questionnaires and computer-based neuropsychological assessments (see Table 1). Participants will receive an EEG recording during one part of the neuropsychological assessment, namely during a modified Go/No-Go paradigm including various working memory loads [78] to assess the interaction between working memory load and response inhibition programmed in Presentation® software (Neurobehavioral Systems, Inc., Berkeley, CA, USA). At the Wiesloch study site, EEG recordings are conducted using a mobile EEG system (24 channels with active electrodes; sampling rate 1000 Hz; mBrainTrain, Belgrade, Serbia). At the Mannheim site, stationary EEG assessments are performed using BrainVision Recorder software package (32 channels with active electrodes; sampling rate 1000 Hz; Brain Products GmbH, Gilching, Germany). Two channels are occupied by the tDCS electrodes for both systems (for groups 1,2 and 4: F3 and F4; for group 3: Cz and O1). After completing all assessments, participants receive their first add-on treatment. For the first tDCS session, the tDCS study groups (groups 1 to 3) will receive a 20-min long tDCS with 0.08 mA/cm2, over the respective brain areas. The inhibition training group will perform a go-/no-go training according to Stein et al. [13] and the sham group will receive a 20 min long sham tDCS. Before and after the stimulation or training, craving will be assessed (see Table 1).

**Table 1 Tab1:** Measurements and interventions

		T1	T2-T4	T5	T6-7	T8	T9
Baseline information and medical screening	Sociodemographic data	X					
	Internistic, neurological examination	X					
	Drug/pregnancy urine screening	X		X		X	
	Menstrual cycle	X					
	Structured Clinical Interview for DSM-5	X					
	Edinburgh Handedness Inventory (EHI, [79])	X					
Questionnaires Alcohol/Substance	Craving Scale [80] Alcohol Urge Questionnaire (AUQ, [81])	X X	X X	X X	X X	X X	X X
	Fagerstrøm Test of Cigarette Dependence (FTND, [82])	X				X	
	Craving Automated Scale for Alcohol (CAS-A, [83])	X				X	X
	Obsessive Compulsive Drinking Scale (OCDS, [84])	X					
	Alcohol Dependence Scale (ADS, [85])	X					
Questionnaires Clinic	Beck Depression Inventory–II (BDI-II [86]) Quality of life [87]	X X		X		X X	
	Perceived Stress Scale (PSS, [88])	X				X	
	Barratt Impulsiveness Scale (BIS, [89])	X		X		X	
	Creature of Habit Scale (COHS, [90])	X				X	
	ASRS-V1.1 Screener (WHO, 2004) Childhood Trauma Questionnaire (CTQ, [91])	X X					
Outcome consumption	Form 90 interview [92]	X		X	X	X	X
	Time to relapse	X		X	X	X	X
	Percentage of abstinence/heavy drinking days	X		X	X	X	X
Neuropsychological assessment	Delay Reward Discounting Task [93]	X		X		X	
	Dimensional Card Sorting Task [94]	X		X		X	
	Dot-probe task [95]	X		X		X	
	Stop-signal task [96]	X		X		X	
Electroencephalography (EEG)	Modified Go/NoGo paradigm [78]	X		X		X	
Interventions	TAU + active tDCS (Groups 1–3)	X	X	X			
	TAU + sham tDCS (Group 4)	X	X	X			
	TAU + computerized inhibition training (Group 5) TAU (Group 6)	X X	X X	X X			
	Adverse events	X	X	X			

*T1* = *first investigation day, T2-4* = *second to fourth investigation days, T5* = *fifth investigation day, T6-7* = *follow up after 4 weeks (T6) and 8 weeks (T7) *via* phone, T8* = *follow up after 12 weeks on site, T9* = *follow up after 24 weeks *via* phone*

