### Experimental procedure

*N* = 162 SUD patients, who voluntarily enter a qualified detoxification treatment program, will be examined (inpatient or day-clinic setting) at the Department of Addictive Behaviour and Addiction Medicine at the Central Institute of Mental Health in Mannheim, Germany and the Clinic for Addiction Therapy and Withdrawal at the Psychiatrisches Zentrum Nordbaden in Wiesloch, Germany. A randomized assignment (block randomization with permuted blocks of size 12) to one of six groups will be performed. All participants will be included during their second week of hospital stay to ensure completed detoxification (at least 7 days of abstinence) and enrollment in the treatment as usual (TAU). TAU comprises an at least three weeks long therapy duration including medical and therapeutic treatment. We will follow a placebo-controlled single-blind study design, in which participants do not receive any information about electrode placement or active vs. sham condition, except in the non-tDCS groups, namely group 5 (inhibition training) and group 6 (TAU).

Four groups will receive 20-min tDCS sessions using the Sooma Duo™ device (Sooma Oy, Helsinki, Finland) over five consecutive days at an intensity of 2 mA (≈0.08 mA/cm^2^). Electrodes (25 cm^2^) will be placed using a standardized EEG cap following the 10–20 system to ensure consistent positioning across sessions [44]. The current will be ramped up from 0.3 mA to 2 mA at 0.1 mA/s, maintained for 20 min during active stimulation. Stimulation sites will differ by group:

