### Statistical analyses

The behavioral and EEG results of the inhibitory control paradigm [78] and craving ratings are defined as primary outcome measures. The results of the inhibitory control paradigm will be compared between testing days before (T1) and after fifth (T5) stimulation or training and after a follow-up period of 12 weeks (T8). Craving rates will be compared before and after the first stimulation/training (T1) and across the subsequent stimulation/training sessions (T2-T5), as well as during the follow-up period (T6-T9). Secondary outcomes include duration of abstinence and amount of substance consumed during the follow-up period.

Regarding the EEG data, resampling (to 250 Hz), filtering (70 Hz high- and 0.1 Hz low-pass filter; 50 Hz notch filter), re-referencing to an average reference, manual inspection, independent component analyses, and segmentation (from –200 to 1200 ms) will be conducted. Removed channels due to technical and regular artifacts (e.g., movement artifacts, excessive noise) will be interpolated using neighboring electrodes. ERP components will be scored as mean amplitudes between 200–300 ms and 300–500 ms over fronto-central and central-parietal electrodes for the N200 and P300 components, respectively. All data (EEG, neuropsychological and psychometric data) will be analyzed using t-tests, repeated measures analysis of variance (rmANOVA) and Pearson correlations. The influence of treatment modality (tDCS add-on intervention over various locations versus inhibition training versus standard treatment) on relapse will be tested with a Cox Regression (outcome variable: time until first relapse). Due to the included individuals and the matched-group design, potential influencing factors on primary and secondary endpoints (e.g., type of substance, severity of SUD, number of comorbidities) will be included in the analyses as covariates. In secondary analyses, we will also take a closer look at the potential influence of these factors on treatment response. In this way, it might be possible to identify subgroups that respond particularly well to the treatment (‘treatment responders’) with the goal of precision-targeted treatments for addiction. Statistical analysis will be conducted using SPSS (IBM Corp., Armonk, N.Y., USA).

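### As printed, the T1 Go/No-Go EEG uses a group-dependent electrode layout before the first treatment, so montage class is known at baseline and the available EEG channels differ by arm

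*Protocol article*

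**What the plan says.** All references are to the Protocol article.

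- **Randomisation** (Experimental procedure): "A randomized assignment (block randomization with permuted blocks of size 12) to one of six groups will be performed". The time at which allocation is made or opened is not given.
- **Eligibility** is settled on T1 itself (first-day text after Fig. 1): "Subsequently, diagnostic interviews will be performed to assess eligibility for study participation".
- **EEG set-up**, in the same T1 paragraph, after the descriptions of the two sites' recording systems: "Two channels are occupied by the tDCS electrodes for both systems (for groups 1,2 and 4: F3 and F4"; for group 3 the sites are Cz and O1. Nothing is said of groups 5 and 6.
- **Order**, in the sentence that follows: "After completing all assessments, participants receive their first add-on treatment".
- **Blinding** (Experimental procedure) is single-blind: "participants do not receive any information about electrode placement or active vs. sham condition, except in the non-tDCS groups". Those groups are the inhibition training and TAU arms.
- **Use of T1** (Statistical analyses): the Go/No-Go results, behavioural and EEG, are primary together with craving. The Go/No-Go results are "compared between testing days before (T1) and after fifth (T5) stimulation or training" and again at T8.
- **ERP scoring** (Statistical analyses): the N200 is averaged over fronto-central sites and the P300 over central-parietal sites, after average re-referencing. The individual electrodes are not listed.

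**The concern.** A baseline should be measured before anyone involved can act on the allocation, and in the same way in every arm. The T1 text, taken in order, does neither for the Go/No-Go and EEG outcome.

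There are two separate consequences. First, staff running the baseline would know which layout class a participant is in, and participants outside the tDCS arms might work out that they will not be stimulated. T1 is the reference for the T5 and T8 comparisons. A response to that knowledge at T1 would therefore enter the group-by-time effect with its sign reversed, and adjusting for a baseline affected by allocation does not reliably remove it. Second, the recording itself differs by arm, because different scalp sites are lost in different groups. This does not depend on anyone's expectations.

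**Working it through.** The plan gives no figure on this point. The check is of sequence, with simple counts.

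**1. Sequence at T1.** The text runs: information and consent; eligibility interviews and tests; questionnaires and neuropsychological tasks, with EEG during the Go/No-Go task; the statement of which channels the tDCS electrodes occupy, by group; then first treatment after all assessments. Electrodes cannot be positioned by group unless the layout class is known. So, as written, that class is known before the baseline recording.

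**2. What the layout reveals.** Group sizes come from the Sample size section: 27 per group, 6 × 27 = 162.

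| Layout at T1 | Groups | Participants | Share |
|---|---|---|---|
| F3/F4 occupied | 1, 2, 4 | 3 × 27 = 81 | 81/162 = 50.0% |
| Cz/O1 occupied | 3 | 27 | 27/162 = 16.7% |
| Not stated | 5, 6 | 2 × 27 = 54 | 54/162 = 33.3% |

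Right anodal, left anodal and sham share one layout. The layout identifies group 3 and, if groups 5 and 6 wear no tDCS electrodes, separates those two from the rest. It does not separate groups 1, 2 and 4 from one another.

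**3. Channels.** Two lost channels are 2/24 = 8.3% of the Wiesloch system and 2/32 = 6.3% of the Mannheim system. Location matters more than number: Cz is a central site, and F3 and F4 are frontal. If any of them is among the scored sites, the N200 or P300 is averaged over different electrodes in different arms. With an average reference, the missing sites also change the reference.

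**4. Across visits.** Table 1 places the EEG at T1, T5 and T8, and tDCS at T1 to T5 only. At T5 the assessment follows the fifth session, so the sites may still be occupied. At T8 there is no tDCS. The channel set can therefore also change within a person.

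**5. Size of an expectation effect.** Let s1 be the shift that knowledge of the arm causes at T1 in groups 5 and 6, and s5 the shift at T5. The change from T1 to T5 in those groups moves by s5 − s1. If allocation is opened after baseline, s1 = 0 and the movement is s5. The documents give neither value. As an illustration only, assume s1 = 0.2 SD:

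- no persistence (s5 = 0): 0 − 0.2 = −0.2 SD
- half persists (s5 = 0.1): 0.1 − 0.2 = −0.1 SD
- full persistence (s5 = 0.2): 0.2 − 0.2 = 0

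The net distortion cannot be sized from the documents.

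**The case against.** The strongest reply is that the time of randomisation is not stated, that an article may leave it to the full protocol, and that the channel sentence may be a general equipment note. It follows the descriptions of both EEG systems, and occupied channels would be expected at T5, where recording follows stimulation. That reading is possible, so a baseline taken after allocation remains an inference. However, the sentence cannot be a note on every recording, because T8 has EEG and no tDCS. It also stands in the T1 paragraph, directly before the sentence that puts treatment last. On either reading the text needs correcting.

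Several stronger conclusions might be drawn, and the documents do not support them:

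- *Staff know the full allocation at baseline.* The shared F3/F4 layout shows neither polarity nor active versus sham.
- *Groups 5 and 6 see their allocation before baseline.* Their set-up is not described. They may infer it if they wear no tDCS electrodes. They are openly unblinded in any case, so the only new issue is learning the arm before baseline rather than after.
- *Baseline craving is affected.* Craving is rated before and after the session, but the text does not place the first rating before or after cap fitting.
- *The primary contrasts move by a known amount.* Step 5 of the working shows that a persistent shift cancels in the change score.

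It is also fair to object that changing only the T1 layout could create a difference in channels between T1 and T5 within the same person. That objection stands, and the fix has to cover all three EEG visits.

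**Conclusion.** The point holds in limited form. As written, the T1 Go/No-Go EEG is recorded with a layout that depends on group, before first treatment. At least the montage class would be known to staff at the baseline of a primary outcome, and the 54 participants in groups 5 and 6 may be able to infer their arm. The channels available for the two ERP components differ between groups 1, 2 and 4 (81 participants) and group 3 (27); those for groups 5 and 6 are unstated.

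This rests on reading the T1 paragraph in order, and for groups 5 and 6 on the assumption that they wear no tDCS electrodes. The channel difference changes the ERP scores only to the extent that occupied sites enter the scoring or the reference. An effect on craving is possible but not shown. Neither the size nor the direction of any net bias can be given. The change is worth making because it is cheap and protects the reference value of a primary outcome, not because a bias has been demonstrated.

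**What to change.** 1. State that allocation is opened only when all T1 baseline measures are complete: questionnaires, pre-session craving, neuropsychological tasks and EEG.
2. Fit the tDCS electrodes after the T1 recording. If the channel sentence was meant for T5 only, move it there, and say what groups 5 and 6 wear.
3. Score the N200 and P300 from one named channel set that is the same in all six arms and at T1, T5 and T8, for example by leaving F3, F4, Cz and O1 out of the scoring for everyone. Apply the same set when forming the average reference.

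**Cost.** The T1 visit becomes somewhat longer, because electrodes are fitted after the recording. Up to four channels are lost from ERP scoring: 4/24 = 16.7% at Wiesloch and 4/32 = 12.5% at Mannheim. No new data or staff are needed. Changing the T1 layout without item 3 would risk replacing a difference between arms with a difference between visits.

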#### Days 2 to 4 (T2-T4; duration ca. 40 min)

Participants will either continue with TAU (group 6), receive a 20-min long tDCS (groups 1–3), a ca. 20-min inhibition training (group 4), or a 20 min long sham tDCS (group 5) for each of the following three days (e.g., Tuesday, Wednesday, Thursday) in addition to their standard treatment. Craving will be assessed after each session. Adverse events are systematically assessed throughout the add-on treatment period. At the beginning of each investigation day, participants are asked about any adverse events that occurred since the previous session.

#### Day 5 (T5; duration ca. 1 h)

Participants will receive the fifth and last 20-min long tDCS (groups 1 to 3), sham tDCS (group 4), or an inhibition training (group 5) (e.g., Friday). Following, the same computer-based neuropsychological assessment will be completed (T3), and craving will be re-assessed. A full list of assessments is provided in Table 1. Adverse events that occurred since T4 are documented at the beginning of the investigation day. As participants are not contacted again until 28 days after T5 for the first follow-up assessment, any adverse events related to the final session are assessed and documented at the end of the T5 assessment.

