Group 1: Anode over right DLPFC (electrode position F4), cathode over left DLPFC (electrode position F3)Group 2: Anode over left DLPFC (electrode position F3), cathode over right DLPFC (electrode position F4)Group 3: Anode over occipital cortex (electrode position O1), cathode over electrode position Cz.Group 4 will receive sham stimulation (anode over electrode position F3, cathode over electrode position F4). For blinding, the current will ramp up to 2 mA and then immediately ramp down to 0 mA, mimicking the sensation of active stimulation while avoiding physiological effects. With respect to sham tDCS as a control condition, a strong and possibly heterogonous placebo effect is still under discussion. This effect may also be due to using short, active stimulations at the beginning of a sham tDCS that could induce neurophysiological changes [75]. However, an active sham condition will improve blinding of the participants towards the intervention as switching off the current does not represent a reliable sham [77].Group 5 receives a computerized inhibition training using a go-/no-go-task with individually adapted, alcohol-related stimuli, as described in Stein et al. [13].Group 6 receives only TAU but follows the same study protocol with respect to all measurement timepoints; however, there is no contact from T2 and T4. During the follow-up period of 24 weeks, a total of one personal and three telephone contacts are planned. All participants will be contacted after 4, 8, and 24 weeks via telephone and possible relapses and amount of substances consumed will be assessed in a self-reported manner. For the third follow-up after 12 weeks, all participants will be invited for a personal follow-up assessment (timepoint T8). See Figure 1 for further details.

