### Risks and strengths of the study

Risks regarding successful study completion primarily include dropouts and relapse. Study completion will be possible in case of relapse, to not only reduce the threshold for participants to keep in touch, but to additionally examine the aspect of harm reduction, namely reduced substance consumption in the absence of abstinence. Stepwise reimbursement is intended to support participation during the follow-up period.

The advantages of this study outweigh the risks. tDCS is a mobile, low-cost, and easy-to-administer technique, with potential for at-home use post-discharge. Devices enabling self-stimulation of the DLPFC are already available and require no specialized training. Notably, tDCS has been established as a safe, well-tolerated adjunct treatment for depression [99], and may hold promise for SUD treatment. However, more evidence is needed to support its clinical application in an addiction context. Although alcohol-withdrawing individuals may have a lower seizure threshold [100], a review of tDCS safety has not identified any serious adverse effects for conventional tDCS protocols (≤ 40 min, ≤ 4 mA, ≤ 7.2 Coulombs), even in neurologically vulnerable populations such as those with stroke or epilepsy [101].

Examining individuals with different kind of SUDs allows drawing conclusions regarding general (neuro-)biological mechanisms and treatment options for a large body of affected individuals, not only a small subgroup with a specific SUD. In addition, we will be able to investigate in a large heterogeneous sample whether there are individual factors that influence the treatment response in order to analyze whether the one-size-fits-all approach is appropriate here or whether the approach is particularly suitable for a subset of patients.

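### Adverse events after the fifth session are asked about only before the T5 visit ends, and no follow-up contact carries an adverse-event question

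*Protocol article*

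**What the plan says.** In the Protocol article, the section on Days 2 to 4 sets the general rule: "Adverse events are systematically assessed throughout the add-on treatment period". It then gives the timing: "At the beginning of each investigation day, participants are asked about any adverse events that occurred since the previous session". The Day 5 section continues this rule for the interval from T4 to T5.

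The fifth session is handled differently. The Day 5 section gives the reason, "As participants are not contacted again until 28 days after T5 for the first follow-up assessment", and then the rule: "any adverse events related to the final session are assessed and documented at the end of the T5 assessment". The heading of that section puts the visit at about one hour.

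The adverse-event row of Table 1 has marks at T1, T2-T4 and T5 and is blank for T6-7, T8 and T9. The text on the follow-ups names relapse, consumption and craving, with neuropsychology and EEG added at T8. It names no adverse-event item and refers to Table 1 as the complete list.

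For group 6 (TAU only), the Experimental procedure section says that "there is no contact from T2 and T4".

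**The concern.** The rule gives the last session a much shorter period of observation than the four before it, although it comes at the end of the cumulative exposure. The stated reason is the gap of 28 days to the next contact. That gap is a good reason to add a check before the participant leaves. It is no reason to leave the question out of the next contact, which is already scheduled for all six groups.

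The article's section on ethical and legal aspects lists itching, short-term headaches and skin irritation as reported effects of the device. Some of these can start or become noticeable after the participant has left the visit. If the written plan is followed, nobody asks about them. What is at stake is how complete a later statement on tolerability can be.

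A second, separate point concerns group 6. Table 1 and the Days 2 to 4 text show adverse-event assessment at T2-T4 with no exception for this group, while the Experimental procedure section says the group is not contacted then. The two cannot both be carried out.

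**Working it through.** The article states no figure for this point, so there is none to reproduce. The check consists of setting the rules side by side and simple counts.

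**Inputs.** 27 participants per group (Sample size); five sessions on consecutive days and 20 minutes per session (Experimental procedure); T5 visit of about 1 h (Day 5 heading); next contact 28 days after T5 (Day 5 text); adverse-event marks in Table 1.

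**Observation window by session.**

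| Session | When asked | Time covered after the session |
|---|---|---|
| 1 to 4 | start of the next investigation day | about 24 h (assumes consecutive daily visits) |
| 5 | end of the same visit | at most about 60 − 20 = 40 min, if the stated hour includes the session |

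Four weeks × 7 days = 28 days, so the article's two descriptions of the T5 to T6 interval agree.

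**Sessions affected, at full enrolment.**
- Active tDCS: 3 groups × 27 × 5 = 405 sessions, of which 3 × 27 = 81 are final sessions. 81/405 = 20%.
- Sham: 27 × 5 = 135 sessions, of which 27 are final sessions. 27/135 = 20%.
- Together: 108 of 540 sessions, again 20%.

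These are upper limits, because dropout before T5 lowers them. With the 25 per group that the sample size section aims to retain, the counts are 3 × 25 = 75 active and 25 sham.

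**Follow-up.** Of the four contacts T6, T7, T8 and T9, none carries an adverse-event item in Table 1 or in the text.

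**Group 6.** Groups 1 to 5 have five adverse-event contact days (T1, T2, T3, T4, T5). If the phrase on group 6 means T2 to T4, that group has two (T1 and T5). If it means only T2 and T4, it has three. The Day 5 text has events since T4 recorded at the start of T5. Read literally, that look-back does not cover T1 to T4 for a group that was not seen at T4.

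The number of events missed cannot be derived, because the article gives no event rates or onset times.

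**The case against.** The strongest case on the other side has five parts.

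- **The rule is a deliberate choice with a stated reason, and the end-of-visit check catches immediate effects.** This stands as far as it goes. The check should be kept, and the article does not contradict itself about T5.
- **Adverse events are neither a primary nor a secondary outcome.** This stands. A reader might infer that the rule makes tDCS and TAU event rates non-comparable and so damages a planned analysis. The article plans no comparison of adverse events between arms, and the T5 cut-off falls at the same point in every arm. The difference in contact days for group 6 is real, but it comes from the separate statement about T2 to T4.
- **The seizure argument is weak.** A reader might lean on the remark that "alcohol-withdrawing individuals may have a lower seizure threshold". In the section on risks and strengths this is only the concession. The main clause reports that a safety review found no serious adverse effects of conventional tDCS, within limits that include 7.2 C. The planned session delivers 0.002 A × 1,200 s = 2.4 C, ignoring the ramp. Epilepsy and marked withdrawal symptoms are exclusions. The point does not need this argument.
- **Events need not be lost.** This stands in part. Participants enter in the second week of a treatment lasting at least three weeks, so clinic staff may notice later events. Rules for spontaneous or serious-event reporting may be in the full protocol, which is not shown. A reader might infer that later events are never recorded; the article shows only that no query is scheduled.
- **A question at T6 does not equalise the sessions.** This stands. It replaces a very short window with a 28-day recall period, in which attribution to the session is weaker. That is a reason to report the answers separately, not to leave the question out.

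**Conclusion.** The point holds as a cheap improvement to the safety record. After the fifth session, adverse events are asked about only until the end of a visit of about one hour. After sessions 1 to 4 they are asked about on the next day, and none of the four follow-up contacts asks at all. Delayed effects of the last session have no scheduled query. This concerns 20% of sessions: at most 81 active and 27 sham final sessions at full enrolment.

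The conclusion assumes that Table 1 is the complete schedule, as the article says, and that sessions fall on consecutive days. It does not say that events go wholly unnoticed, nor how many would be missed.

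The group 6 discrepancy is a second, independent point: the article schedules adverse-event assessment at T2-T4 without exception and also says that this group is not contacted then.

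No efficacy result and no sample size figure is affected.

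**What to change.** 1. Keep the check at the end of T5.
2. Add one adverse-event question, covering the time since T5, to the T6 telephone call for all six groups, and mark it in the adverse-event row of Table 1.
3. Report the T6 answers separately from the next-day reports, since they rest on four-week recall and a different window.
4. Reconcile the statement that group 6 has no contact from T2 to T4 with Table 1 and the Days 2 to 4 text. At T5, ask group 6 about the whole period since T1.

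The cost is about a minute per call, one extra question at T5 for group 6, and edits to Table 1 and the text. No new contact is needed. The remaining weakness is recall over four weeks, which the separate reporting makes visible but does not remove.
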